### Trial status

This is the first version of the protocol (March 4 2025). Recruitment started in October 2024. End of recruitment is anticipated in April 2025.

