### Trial design {8}

This study employs a multiple baseline single-case experimental design (SCED). In a SCED, each case (i.e. each individual) serves as its own control, facilitated by intensive longitudinal data collection in two phases: Phase A (baseline) and Phase B (intervention) [36]. Randomisation of intervention start mitigates potential confounding of time due to external factors (*history*, e.g. transition from winter to summer*)* and internal factors (*maturation*, e.g. spontaneous recovery) [37]. This enhances internal validity [38], as does studying the effect across individuals with a multiple baseline design [38, 39]. Change relative to the randomised intervention start moments allows for causal inference within a SCED. Therefore, in this study, multiple participants start the Booster intervention at a randomised point in time to allow investigation of causal relationships between the intervention and study outcomes at the group level. Data is collected daily for 130 days (nearly nineteen weeks) with ESM via the Booster app on the participants’ phones.

ESM is also known as ecological momentary assessment (EMA). ESM is a validated structured diary method integrated into daily life [40]. It captures personal experiences and behaviours along with real-time fluctuations in well-being through repeated surveys over a period ranging from several days to weeks [41]. In the following sections, the ESM use is detailed, both the daily ESM for measuring study outcomes in the daily progress monitor and the intensive ESM for personalised insight in fatigue. Based on the Internal Validity subscale of the 15-item Risk of Bias in *N*-of-1 Trials (RoBiNT) Scale, our study design has fair methodological rigour (Suppl. Table 1) [38, 42]. Examples of factors strengthening the internal validity are the long intensive longitudinal data collection and the measurement of intervention adherence. SPIRIT reporting guidelines were followed in this protocol [43]. An overview of the study design is given in Fig. 1 (Suppl. Fig. 1 for more details).

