##### Stage 2: Measurement Period

For four weeks, the participant receives the intensive personalised ESM-survey five times daily via the Booster app with an approximate three-hour interval. The first survey of the day arrives at 9 AM, 10 AM, or 11 AM, based on the participant’s schedule choice during the Start Conversation. The exact timing of notification is randomly assigned within 30 min of the scheduled times. In case of non-response, reminders are sent after 20 and 60 min. After 90 min without response, the survey closes and is marked as missing. Completing the intensive ESM-survey costs less than one minute.

From PROfeel research [34], we know that a compliance of at least 35% (i.e. 49 completed surveys) is required to derive a Booster Report. Yet, the reliability of the output increases as the number of completed surveys does. Therefore, in line with previous research [48], we aim for at least 70% compliance. Extension of the Measurement Period will be offered to the participant in case of < 70% compliance. If the participant does not want to extend the Measurement Period, the researcher must discuss the content of the report with more caution because of the lower reliability (see section “Stage 3: Insight Conversation”).

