##### Stage 3: Insight Conversation

After the four-week Measurement Period, the participant has a face-to-face conversation with the investigator. The Booster report, based on the intensive ESM-surveys, is discussed and lifestyle goals are set using shared-decision making.

**Creating the Booster reportCreating the Booster report** A statistician, blinded to the participant, uses the intensive ESM surveys to compute an individual statistician report. This contains a summary of fatigue-sustaining factors and their dynamic networks. The summary includes fluctuations across the whole assessment period, averages for assessment hour and day of the week, differences for categorical factors, and day-to-day associations between paired ESM items across the Measurement Period. The dynamic networks (vector autoregression lag 1) are produced using Residual Dynamic Structural Equation Modelling. This method corrects for moving weekly average trends, weekend, and time of day and has been described more elaborately elsewhere [24, 48–50]. From all the generated output, the statistician and investigator independently select the most relevant summary figures and dynamic networks to be included in the Booster report (Fig. 3). Relevance is based on statistical significance, magnitude of standardised estimates, and assumed usefulness for the participant. Possible differences between selections are settled via discussion between the statistician and investigator.

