##### Stage 4: Experiment Period

In the twelve-week Experiment Period, the Booster app aids goal attainment with evaluations added to the daily progress monitor on self-selected goal days. If the active goal is not reached multiple times, the app proposes to change or adapt the goal. The participant can adapt the active goal or change it to another goal.

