### Sample size {14}

The power to detect an intervention effect with a multiple baseline design (RQ1) depends on the autocorrelation of consecutive daily progress monitor measurements, the start moment range, the number of repeated measurements, the intervention effect, and the number of cases [52]. In the earlier PROfeel study [48], the median autocorrelation of weekly measurements was 0.17 for FSE, 0.30 for fatigue severity, and 0.09 for QoL. Median autocorrelation of the five times daily ESM item on fatigue severity was 0.37 [48]. We expect the daily measurements in this study to show a higher autocorrelation than weekly measurements, but lower than a five times daily item. Thus, we assumed the autocorrelation in our study to be 0.30 across outcomes. The start moment range is nine, as the Booster intervention is randomised to start (T1) ten to eighteen days after the start of the daily progress monitor (T0). With 100% compliance, the number of repeated measurements is 130. With the abovementioned assumptions and inclusion of twenty cases, with up to 30% of daily measurements missing, the multiple baseline single-case randomisation test (SCRT) can detect medium to large intervention effects of ≥ 0.7 with a power of ≥ 0.80 at the group level (RQ1, Table 1). However, we anticipate small intervention effects since Booster is an early intervention, not treatment. The SCRT, used in SCED, has limited power to detect such small intervention effects [37, 52, 53]. In contrast, the permutation distancing test (PTD), developed for testing differences in means in single-case observational designs (SCODs), exhibits higher statistical power [53]. It is important to note that SCOD cannot establish causality. With the abovementioned assumptions, with up to 40% of daily measurements missing, the study is well powered to observe changes in outcomes for effect sizes as small as 0.3 at the single-case observational level (RQ2, Table 1).

**Table 1 Tab1:** Power for detecting intervention effects at the group and single-case level

Factors influencing power	Study design	
Autocorrelation (%)	30	
Repeated measurements (*n*)	130	
Power (%)	≥ 80	
Cases (*n*)	20 (group level)	1 (single-case)
Test	Multiple baseline SCRT	PDT
Start moment range (*n*)	9	NA
Maximum percentage missing data to retain sufficient power (%)	30	40
Minimum detectable effect size	0.7 (medium to large)	0.3 (small)

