### Data collection and management

#### Plans for assessment and collection of outcomes {18a}

Study outcomes will be assessed using the daily progress monitor, a repeated survey. The Booster app sends the daily progress monitor at a random time within the hour before bedtime. Participants determine the exact timing of completing the monitor, provided it is within three hours of receiving the notification. Responses not submitted within this three-hour window are considered missing. For each item, participants are asked to reflect on their day. Item order is randomised to minimise method bias [56]. The daily monitoring period starts ten to eighteen days before the Start Conversation and continues for 130 days, ending twelve weeks into the Experiment Period.

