#### Other study outcomes

*Fatigue severity* will be measured with the four-item pSFQ, answered on a seven-point Likert scale from “Yes, that is correct” to “No, that is not correct” [45]. The pSFQ score ranges from 4 to 28, with higher scores reflecting more severe fatigue. It has good psychometric properties, including Cronbach alpha’s ranging from 0.84 to 0.94 [45]. In the official pSFQ, respondents are instructed to think of the past two weeks. For the daily progress monitor in this study, the instruction was adapted to think of today.

*Participation* will be measured as school or work presence, which is calculated by the hours present divided by the hours scheduled multiplied by 100. For each working or school day, participants will fill in the number of hours on their personal timetable and the number of hours attended. This item is adapted from the PROactive cohort study [57].

*Life satisfaction* will be measured with the Cantril Ladder, adapted for adolescents [58]. Respondents rate their life with a ladder numbered from zero to ten. The bottom represents “The worst possible life”, and the top ‘The best possible life”. This version of the Cantril Ladder is extensively used in the Netherlands. It has good reliability and convergent validity with other well-being measures [58].

*Perceived health* will be measured with the EuroQol (EQ) visual analogue scale (VAS) [59]. Respondents rate their current health on a vertical scale from 0 (“The worst health you can imagine”) to 100 (“The best health you can imagine”). The scale shows the exact number selected. Rating their health status is feasible for adolescents, and EQ-VAS scores can predict health-related QoL as measured by the EQ Five Dimensions Health Questionnaire (EQ-5D) [59].

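### For participants enrolled from about March, part of Phase B falls in the summer school break, and the single-case analyses (RQ2 and RQ3) have no term to separate a break effect from Booster

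*Protocol article*

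**What the plan says.** - **Calendar.** Trial status: "Recruitment started in October 2024. End of recruitment is anticipated in April 2025". The daily monitor "continues for 130 days, ending twelve weeks into the Experiment Period".
- **Stages.** "The start moment range is nine, as the Booster intervention is randomised to start (T1) ten to eighteen days after" the daily monitor begins (Sample size). The Measurement Period then lasts four weeks: "For four weeks, the participant receives the intensive personalised ESM-survey five times daily". The Experiment Period lasts twelve: "In the twelve-week Experiment Period, the Booster app aids goal attainment".
- **Phase B.** Under RQ1, FSE is expected to change at the Insight Conversation, fatigue four weeks later, and life satisfaction and perceived health six weeks later.
- **History.** Trial design names the move from winter to summer as an example and says: "Randomisation of intervention start mitigates potential confounding of time due to external factors".
- **Single-case tests.** The PDT compares phase means. The ITSA fits an intercept and slope per phase with autocorrelation. Wild Binary Segmentation then looks for change points. None is described with a term for school term or break.
- **Use of the results.** RQ2 says that neither the PDT nor the ITSA can directly establish causality. RQ3 nevertheless expects change points to show which Booster stages mattered. The Discussion says that PDT effects which replicate across individuals and match the timing of stages support efficacy.
- **Data at hand.** On participation: "For each working or school day, participants will fill in the number of hours on their personal timetable". For the model behind the Booster report: "This method corrects for moving weekly average trends, weekend, and time of day".

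**The concern.** The randomised start deals with calendar effects only through a test that re-randomises it, which is the group-level SCRT. Within one participant the start is a single fixed date. If term ends inside Phase B and outcomes move because of that, the PDT sees a difference between phase means and the change-point method sees a step.

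Such a shift is plausible on the article's own terms, because Stage 1 gives school pressure as an example of a factor that sustains fatigue. The size of any shift is unknown.

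At stake is how RQ2 and RQ3 are read. Some spring enrolees could be counted as changed because school stopped. Because they share one calendar event, their changes could also look like replication, which is part of what the Discussion relies on.

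**Working it through.** **1. Length of the series.** Let s be the randomised baseline, 10 to 18 days. Total = s + 28 + 84 = 122 to 130 days. The stated 130 is reproduced with the longest baseline.

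**2. Calendar span.** Take the recruitment window as 1 October 2024 to 30 April 2025, which is 212 days. A participant starting on 30 April 2025 ends on 29 August (122 days) to 6 September 2025 (130 days).

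**3. Who is affected.** Assumptions not in the document: a six-week (42-day) break starting between 5 and 19 July 2025, and even enrolment. A series touches the break if T0 + (s + 112) − 1 reaches the break start, so the first affected T0 is the break start minus (s + 111) days.
- s = 18, break from 5 July: 5 July − 129 days = 26 February. Affected days to 30 April = 64; 64/212 = 30%.
- s = 10, break from 19 July: 19 July − 121 days = 20 March. Affected days = 42; 42/212 = 20%.
- With 20 participants this is about 4 to 6.

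**4. How much of Phase B is affected.** Phase B has 84 days for FSE, 84 − 28 = 56 for a four-week lag and 84 − 42 = 42 for a six-week lag. Counting break days for each enrolment day, over s = 10 to 18 and break starts 5 to 19 July:

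| Outcome | Largest share of Phase B in break | Share of window with at least half of Phase B in break | Break days in Phase A, T0 on 30 April |
|---|---|---|---|
| FSE | 42/84 = 50% | 0.5 to 11% | 0 |
| Four-week lag | 42/56 = 75% | 7 to 17% | 0 to 8 |
| Six-week lag | 42/42 = 100% | 10 to 20% | 0 to 22 |

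The 100% is nearly an empty cell. Overlap of 90% or more occurs on 5 to 9 of 212 enrolment days (2 to 4%), which is less than one participant in 20.

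**5. What a break effect does to a phase-mean test.** Series were simulated with no Booster effect, AR(1) autocorrelation 0.30 (the article's planning value), 30% of days missing and a two-sided 5% generalised least squares test of phase. Half of Phase B lay in the break.
- Six-week lag, break shift 0.3 / 0.5 / 0.8 SD: about 8 / 14 / 28% flagged as change.
- FSE: about the same. With a break indicator in the model the rate falls to about 5%.

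**6. A closer stand-in for the planned tests.** A block permutation test resembling the PDT, and an ITSA with phase intercepts and slopes, were run for T0 on 30 April with a 14-day baseline, a break starting 12 July, no missing days and a shift of 0.7 SD.
- Permutation test: 27% (FSE), 62% (four-week lag), 42% (six-week lag), against 8 to 9% with no break effect.
- ITSA level term: 5%, 33%, 22%, against 7 to 8%.

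The null rates of this second check are somewhat above 5%, so it shows direction only. No change-point method was simulated.

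**The case against.** The other side has several good points.

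- **Causality is already disclaimed.** Trial design ties causal inference to the group level, and Sample size, RQ2 and the Discussion all say that single-case results are not causal. This stands, so the Trial design statement needs no edit. What remains is that RQ3 and the Discussion still draw support for Booster from timing and replication.
- **Interviews ask about external factors.** The Qualitative evaluation covers them and is meant to help interpret single-case results. This is a real safeguard, but it does not adjust a test or a change-point date.
- **Most participants are untouched.** Some 70 to 80% have no summer overlap, and the break falls on a different study day for each enrolment date. A change point may therefore land on the break and expose it. That works only if break dates are set beside the change points.
- **The shift and the break dates are assumed.** This stands.
- **An article may leave exploratory covariates to a fuller plan.** This is fair in general. Here the article sets out the single-case analyses and the inference to be drawn from them, and that inference is the issue.

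A reader might infer three stronger things that the document does not support. First, that the latest enrolees have all of their lagged Phase B in the break and all of Phase A in term. In fact near-complete overlap is rare, and the latest enrolees can have break days in their lagged Phase A. Second, that the RQ4 responder comparison is seriously biased. It classifies on FSE alone, for which overlap never exceeds half. Third, that participation would show a false level shift. It is scored only on school or work days, so the problem there is few scored Phase B days.

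**Conclusion.** The point holds for RQ2 and RQ3, at moderate size. About 20 to 30% of participants would have some Phase B time in the summer break. For about 10 to 20% of the enrolment window, at least half of Phase B for the six-week-lag outcomes lies in it. In those series a phase-mean comparison can flag change at roughly 8 to 28% instead of 5%, depending on the shift. The ITSA level term is little affected for FSE but can be affected for the lagged outcomes when the break begins close to the start of Phase B.

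These figures rest on an assumed six-week break starting 5 to 19 July, even enrolment, shifts of 0.3 to 0.8 SD and a least-squares stand-in for the PDT. The group-level SCRT is not in question.

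**What to change.** - Derive a day-type indicator (school or work day, weekend, school break) from calendar date and the participation item.
- Include it in the ITSA.
- Repeat the PDT on values adjusted for it, as a sensitivity analysis.
- Mark break dates on the change-point results before linking any change point to a Booster stage.
- Where an outcome's Phase B lies almost wholly in the break, report that outcome for that participant as not separable from the break.
- For participation, report the number of scored Phase B days.

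Restricting the analysis to school or work days is not advised, because it would remove most of the lagged Phase B data in the very cases affected.

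The cost is one derived variable and some analysis wording, with no new data and no change to the design. Intervals will be wider for a few spring enrolees.

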## Data Availability

Data will be available after publication and for at least one year after the end of the eHealth Junior Consortium. Data will remain available until the end of 2040. For more information, see section “Confidentiality”.

## Abbreviations

EMA: Ecological momentary assessment
EQ: EuroQol
EQ-5D: EQ Five Dimensions Health Questionnaire
ESM: Experience sampling methodology
FSE: Fatigue-related self-efficacy
IBD: Inflammatory bowel disease
ITSA: Interrupted time series analysis
JIA: Juvenile idiopathic arthritis
mHealth: Mobile health
PDT: Permutation distancing test
QoL: Quality of life
RQ: Research question
RoBiNT: Risk of Bias in N-of-1 Trials Scale
SCED: Single-case experimental design
SCOD: Single-case observational design
SCRT: Single-Case Randomisation Test
UMC: University medical centre
VAS: Visual analogue scale
WBS: Wild Binary Segmentation
